### 2.2. Trial Design

We propose to conduct a double-blinded randomized controlled clinical trial in patients who have >5 mm of spacing in both maxilla and mandible and cases with skeletal class I coming to the department of Orthodontics and Dentofacial Orthopaedics at Fondazione IRCCS Cà Granda Ospedale Maggiore Policlinico di Milano, SST clinics and Università degli Studi di Bari and Naples Clinica Odontoiatrica. Patients in both arms will receive adhered support and will be monitored more frequently than currently recommended by WHO guidelines. The first arm will undergo a traditional method of managing of closure of spacing by thermoformed aligners, and the second aim will be treated with thermoformed and 3D printed aligners. Eligible patients are randomized to the control arm or the intervention arm with a 1:1 ratio using a blocked randomization scheme. The patients will be followed for 6 months (Figure 1).

There will be an initial assessment with detailed case history, extra-oral and intra-oral examination, and clinical radiographs. A diagnosis and treatment plan will be framed. Pre- and post-operative samples of biofilm and saliva will be collected to determine the inflammatory and immunological response. The bridging and early colonizers such as *Fusobacterium nucleatum* (*F. nucleatum)*, pathogenic species such as *Porphyromonas gingivalis (P. gingivalis)*, microbial communities and the composition of the biofilm will be determined by ELISA and PCR. This will help to answer the questions such as if any infection is present, which bacteria colonize, whether we should use antibiotics, etc. In addition, 16 s-ribosomal RNA signatures for identification of the microbial composition of biofilm structures.

***Baseline information:*** (1) A Patient Measured Outcome Questionnaire (PROM) was completed to determine the impact of oral health on quality of life. The PROMs are dozens of tools that allow you to measure the important results for the patient, for example, cost, symptom relief, quality of care, improved oral health, and overall health. It is evaluated after each intervention. (2) Numerical rating scale (NRS) for measuring the pain of patients before and after the intervention. (3) Periodontal health status will be assessed by basic periodontal examination (BPE), Periodontal screening and recording index (PSR index), Basic Periodontal Examination (BPE) scores, Oral Hygiene Index simplified (OHIS), Saliva (Protease activity in saliva) to determine the immune-inflammatory processes by ELISA and biofilm by polymerase chain reaction (PCR). ***Inclusion criteria:*** The eligible cases will be identified during routine clinical visits. CAT is indicated in cases of slight crowding (1–5 mm), spacing problems (1–5 mm), deep overbites (Class II, div. 2), narrow arches requiring expansion, absolute intrusion (one or two teeth), severe crowding with the extraction of the lower incisor and molars requiring distal tipping. Contraindications are crowding and spacing problems greater than 5 mm, anterior-posterior skeletal problems greater than 2 mm, relationship discrepancies and centric occlusion, severely rotated and inclined teeth, open bite, dental extrusion cases, cases with more missing teeth and teeth with short clinical crowns.

Written informed consent will be obtained before the inclusion of the study. An entry form will be completed to determine the eligibility and to collect the baseline characteristics such as periapical radiographs, panoramic radiographs, models, casts, cephalometric tracings, CBCT scans, etc. Patients will be randomized in thermoformed and 3D clear aligners. All non-extraction cases except third molar extraction will be included. ***Exclusion criteria:*** Patients with deciduous and mixed dentition will not be included, and patients with systemic disease, developmental abnormalities, pregnant patients, mentally retarded patients and immunocompromised patients will not be included in the study.

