### 1.1. Aim 1: Effectiveness and Efficacy of Clear Aligners (Invisalign) in Correcting Malocclusions

The clear aligners were introduced in the 1940s, but due to lack of evidence and promotion, it was not widely practiced and adopted. Later, due to the development of biomaterials in dentistry and 3D technology, it became very much popular. Recently, there have been more expert opinions in favor of clear aligners, and there is a lack of evidence in correcting a wide range of malocclusions [21]. Not many studies described the effectiveness of treatment with 3D and thermoformed clear aligners and its impact on periodontal health, generating doubts among clinicians on the efficacy of the device.

Therefore, a well-designed parallel randomized controlled clinical trial will help to overcome the problem. The spacing >5 mm correcting it by using 3D clear aligners and compared with thermoformed aligners therapy.

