### 2.3. Primary End Point

Five-millimeter space closure: To determine the successful outcome of the 3D and thermoformed aligners, a 5 mm of space closure is considered a successful outcome.Debris Index: (The buccal scores) + (The lingual scores)/(Total number of examined buccal and lingual surfaces).Calculus Index: Calculus Index = (The buccal scores) + (The lingual scores)/(Total number of examined buccal and lingual surfaces).Oral Hygiene Index simplified (OHIS): OHIS estimates the extent and amount of debris and calculus present on the tooth in each quadrant of the mouth. It demonstrates the oral hygiene status of the mouth. It is estimated using the debris index and calculus index provided by Greene and vermillion (1964).Plaque Index: The plaque index estimates the amount of plaque on the tooth surface in each quadrant. 0—Absence of plaque, stain or debris; 1—plaque covering no more than 1/3rd of tooth surface; 2—subtle plaque more than 1/3rd but not more than 2/3rd; 3. Plaque cover more than 2/3rd of the tooth surface.Bleeding Index: A modified Sulcus Bleeding Index (mSBI) will be used to record the bleeding from the sulcus and to determine the inflammation, as it is the early indicator of inflammation (clinically).Basic periodontal examination index (BPE): Periodontal status will be determined using the BPE scoring.Root Resorption: Basic periodontal examination such as hard tissues will be conducted using a combination of bitewing and peri-apical radiographs following selection criteria for dental radiography guidelines.Biofilm/Saliva: Saliva (Protease activity in saliva) to determine the immune-inflammatory processes by ELISA and biofilm (protease activity) by polymerase chain reaction (PCR).Oral microbiome: A standard estimation of the oral microbiome will be carried out using 16S ribosomal RNA gene sequencing analysis.

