## 3. Statistical Analysis

The sample size was calculated using a two-sided test by comparing two independent means of control and test between groups with a statistical power of 0.80, alpha of 0.05, with an allocation ratio of 1:1 using STATA 17.0 statistical software. The mean of space closure of 3 mm in control and 5 mm in the test group with sd for control 2.5 and test 2.0 demonstrated that a sample of a least 22 subjects for both groups must be recruited (a total of 44 patients should be recruited). In order to compensate for the loss of follow-up, an increase in patient number *n* = 70 will be recruited.

A descriptive statistic will be carried out for all the indices before and after intervention with 3D and thermoformed aligners. If the data are normally distributed, a parametric test will be carried out. The non-parametric test will be used for the analysis of data that are not normally distributed. A regression analysis to determine the relationship between the dependent and independent variables and for modeling the future relationship between them.

***Safety measurements and adverse events:*** All patients will be monitored for general health and for serious adverse events related to the drug intervention. General and oral assessment including weight, blood pressure, pulse rate, skin, lymph node size, and thyroid palpation will be recorded. There will be no compensation for any adverse events or withdrawal from the study.

***Challenges and Limitations: Follow-up:*** There are chances that there will be a loss of compliance from the patient. To overcome this problem, the patient will be educated and will increase awareness in regard to the type of treatment receiving and its impact on aesthetics.

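### Spacing above 5 mm is both the entry condition and a contraindication; the 5 mm criterion and planning inputs fit the wider-spacing population, not a single closure measure capped at 5 mm

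*Protocol article*

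**What the plan says.** All references are to the protocol article.

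- **Section 1.1 (Aim 1)** sets the target as "The spacing >5 mm correcting it by using 3D clear aligners", with thermoformed aligners as comparator.
- **Section 2.2, opening paragraph**, describes the trial population as "patients who have >5 mm of spacing in both maxilla and mandible and cases with skeletal class I".
- **Section 2.2, inclusion paragraph**, states "CAT is indicated in cases of slight crowding (1–5 mm), spacing problems (1–5 mm", and adds deep overbite, narrow arches, intrusion of one or two teeth, molars needing distal tipping, and severe crowding treated by extracting a lower incisor. It continues: "Contraindications are crowding and spacing problems greater than 5 mm".
- **Section 2.2, next paragraph**, adds: "All non-extraction cases except third molar extraction will be included".
- **Section 2.3** defines success: "a 5 mm of space closure is considered a successful outcome".
- **Section 3** bases the sample size on "The mean of space closure of 3 mm in control and 5 mm in the test group", with SDs of 2.5 (control) and 2.0 (test), two-sided alpha 0.05, power 0.80 and 1:1 allocation, giving 22 per group.

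The article does not say whether space closure is measured in one arch, in each arch, or summed over both.

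**The concern.** The two spacing rules exclude each other: one requires more than 5 mm, the other stops at 5 mm and treats more as a contraindication. A site applying both would enrol nobody. Sites that each chose one would recruit different populations.

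The choice also affects the primary endpoint. A patient cannot close more space than was present at baseline, so a fixed 5 mm target and a planned mean of 5 mm carry an implicit condition on baseline spacing. The wider-spacing rule meets that condition. The 1–5 mm rule, with one measure per patient, meets it only at its upper limit.

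There is a related problem within the inclusion paragraph. It lists problems other than spacing, and a lower-incisor extraction indication that conflicts with the non-extraction rule that follows. If patients without spacing were randomised on that list, space closure would be undefined for them.

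**Working it through.** **1. Eligibility rules side by side**

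| Place | Spacing |
|---|---|
| Section 1.1 | > 5 mm |
| Section 2.2, opening | > 5 mm, both arches, skeletal class I |
| Section 2.2, inclusion paragraph | 1–5 mm indicated; > 5 mm contraindicated |

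The sets {> 5} and {1 to 5} have no common element.

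**2. Reproducing the stated sample size**

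Inputs from Section 3: difference 5 − 3 = 2 mm; SDs 2.5 and 2.0.

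Normal approximation: n = (1.96 + 0.8416)² × (2.5² + 2.0²) / 2² = 7.849 × 10.25 / 4 = 20.1, so 21 per group.

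With the noncentral t distribution and unequal SDs, power is 0.797 at 21 and 0.816 at 22. The stated 22 per group is therefore correct for its inputs. At 30 per group (the Abstract's figure) the same inputs give 0.92.

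**3. Can these inputs occur under the 1–5 mm rule?**

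Assumption: one closure measure X per patient, between 0 and baseline space, hence at most 5 mm.

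Since 0 ≤ X ≤ 5, X² ≤ 5X, so Var(X) ≤ 5m − m² = m(5 − m), where m is the mean.

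| Arm | Planned mean | Planned SD | Largest possible SD |
|---|---|---|---|
| Test | 5 | 2.0 | √(5 × 0) = 0 |
| Control | 3 | 2.5 | √(3 × 2) = 2.45 |

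The test-arm pair is impossible. The control mean is attainable, but its SD is slightly beyond the limit. Read as normal distributions, the planning inputs put 50% of test and 21% of control patients above 5 mm. A success needs exactly 5 mm at baseline and full closure.

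**4. What this does to power**

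The article gives no baseline distribution, so the following are assumptions. Each patient's closure is drawn from the planned normal distribution (control 3, SD 2.5; test 5, SD 2.0) and limited below at 0 and above at the patient's baseline space. Power is for the unequal-variance t-test at 22 per group.

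| Assumed baseline | Mean control / test (mm) | Difference (mm) | Power |
|---|---|---|---|
| Whole mm, 1 to 5 equally likely | 1.99 / 2.72 | 0.73 | 0.41 |
| Uniform 1–5 mm | 2.04 / 2.76 | 0.72 | 0.47 |
| Uniform 3–5 mm | 2.54 / 3.58 | 1.04 | 0.77 |
| Uniform 4–5 mm | 2.71 / 3.92 | 1.21 | 0.82 |
| All exactly 5 mm | 2.84 / 4.21 | 1.37 | 0.84 |
| Two arches summed, each uniform 1–5 mm | 2.89 / 4.40 | 1.50 | 0.78 |
| Plan (no cap) | 3 / 5 | 2.00 | 0.82 |

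The cap shrinks the difference but also the SDs, so power need not fall.

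**The case against.** The strongest defence is that the inclusion paragraph describes when aligner treatment is indicated in general, and that the trial population is the one stated twice, in Section 1.1 and at the start of Section 2.2. For that population the 5 mm criterion and the planning inputs are coherent. This has weight for the non-spacing problems: the wording speaks of indications, so enrolment of patients without spacing is possible but not certain. It does not remove the spacing conflict. The text stands under the inclusion heading, and read as general guidance it would mean the trial enrols patients whom its own text calls contraindicated.

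A second objection is also sound. The 5 mm cap presumes one measure per patient, yet Section 2.2 speaks of both arches. If closure is summed over two arches of 1–5 mm each, up to 10 mm is available and the limits in step 3 no longer apply. The article does not say which is meant.

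A reader might infer more than the documents support:

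- **That the endpoint and planning means are unreachable.** A patient with exactly 5 mm can reach the criterion, and a control mean of 3 mm is attainable.
- **That no patient in either arm could succeed.** Zero success follows from assuming a continuous baseline that almost never equals 5 mm. With whole-millimetre baselines, the same simulation gives about 4% success in control and 10% in test.
- **That the trial is underpowered.** The low figures belong to baselines spread over the whole 1–5 mm range; other baselines keep power near the plan.
- **That the deep-overbite indication contradicts skeletal class I.** The article labels that indication Class II, division 2, without calling it skeletal, so the conflict is not shown.

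**Conclusion.** The eligibility contradiction is explicit and needs no assumption. It must be resolved before enrolment because the rules cannot be applied as written and the primary endpoint depends on the answer.

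The numerical consequence is conditional. It arises only if the 1–5 mm rule prevails and closure is a single measure limited by baseline space. Then success is confined to patients starting at exactly 5 mm, and the planned test mean and SD cannot occur together. If the wider-spacing rule prevails, this limit does not arise and 22 per group stands. Across the baselines tried, power at 22 per group runs from about 0.41 to 0.84, and is about 0.78 with two arches summed, against a planned 0.82. A loss of power is possible, not demonstrated.

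Which spacing rule is right is a clinical matter that this review does not judge.

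**What to change.** 1. Reconcile Section 1.1 and the two parts of Section 2.2 into one eligibility rule. The investigators decide which spacing range applies. The same edit should settle the status of the listed non-spacing problems and of the lower-incisor extraction indication against the non-extraction rule.
2. State whether space closure is measured per arch or summed over both arches.
3. Randomise only patients with measurable spacing at baseline, so that the primary endpoint is defined for everyone.
4. If any eligible patient can have less than 5 mm on the chosen measure, replace the fixed 5 mm criterion with millimetres closed adjusted for baseline space, or the percentage of baseline space closed at 6 months. Then restate the planning means, SDs and sample size for that population.

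The cost is one amendment before enrolment, and possibly a narrower referral pool if patients without spacing are left out.

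### The trial recruits in Milan, Bari and Naples, but neither the blocked randomisation nor the comparison of arms is stated to use site; stratifying and adjusting by site would gain modest precision at almost no cost

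*Protocol article*

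**What the plan says.** Section 2.2 (Trial Design) of the protocol article places recruitment at "Fondazione IRCCS Cà Granda Ospedale Maggiore Policlinico di Milano, SST clinics and Università degli Studi di Bari and Naples Clinica Odontoiatrica". That is at least three cities. The number of patients expected at each clinic is not given.

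The same section describes allocation in one sentence: "Eligible patients are randomized to the control arm or the intervention arm with a 1:1 ratio using a blocked randomization scheme". It names no stratification factor and does not say whether there is one list or one per clinic.

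Section 3 (Statistical Analysis) sizes the trial as an unadjusted comparison: "The sample size was calculated using a two-sided test by comparing two independent means of control and test between groups". The inputs are a "mean of space closure of 3 mm in control and 5 mm in the test group with sd for control 2.5 and test 2.0". For the analysis it says "If the data are normally distributed, a parametric test will be carried out", with a non-parametric test otherwise. It then adds a regression whose independent variables are not listed.

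Section 2.3 lists, next to space closure, several scores that an examiner grades: debris, calculus, OHIS, plaque, bleeding and BPE.

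**The concern.** Blocking on a single list keeps the two arms equal in total. It does not keep them equal within each clinic. In a trial of 60 to 70 patients spread over three cities, the within-clinic split is the one worth protecting, because treatment planning and the grading of indices by eye or probe can plausibly differ between clinics. An uneven split adds between-clinic variation to the difference between arms.

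If the blocks are instead run clinic by clinic, the split is protected, but a two-group test that ignores clinic then uses a standard error that is too large for the design.

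Either way some precision is given up. Stratification also has to be settled before the first patient is randomised, so a later analysis plan cannot supply it.

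**Working it through.** **Inputs from the article.** Section 3: difference 5 − 3 = 2 mm, SDs 2.5 and 2.0, two-sided alpha 0.05, power 0.80, 22 per arm. Recruitment target: 60 in the Abstract, 70 in section 3. I use 60 for the imbalance figures and show power at 22, 30 and 35 per arm.

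**Assumptions, because the article gives no figure.** Sites of equal size (three of 20, or four of 15), and a site share of outcome variance, r, of 5%, 10% or 20%.

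**Step 1: reproduce the plan's figure.** Pooled SD = √((2.5² + 2.0²)/2) = √5.125 = 2.264 mm. With the noncentral t on 2n − 2 degrees of freedom and noncentrality 2/(2.264·√(2/n)), power is 79.8% at 21 per arm and 81.7% at 22. So 22 per arm is correct for the unadjusted test.

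**Step 2: chance imbalance under one common list.** With 30 of 60 patients allocated to each arm and three sites of 20, every site stays at 12:8 or better only if each has 8 to 12 patients in the test arm. The chance of the opposite is

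1 − Σ C(20,a)·C(20,b)·C(20,c)/C(60,30), over a + b + c = 30 with each of a, b, c from 8 to 12, which is 0.353.

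- Three sites of 20: some site splits 13:7 or worse in about 35% of trials.
- Four sites of 15: some site splits 10:5 or worse in about 58% (same method).
- Using actual blocks of 4 on the common list leaves the three-site figure at 35%, so blocking alone gives no protection within sites.
- If site membership is random rather than fixed at 20, a gap of 6 or more occurs in about 29% of trials on a common list, and in none with blocks of 4 kept by site.

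**Step 3: what the imbalance does to the estimate.** At 30 per arm the standard error of the difference is 2.264·√(2/30) = 0.585 mm. Under a common list, site contributes a chance shift with mean zero and SD of about √r × 0.585:

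- r = 5%: 0.13 mm
- r = 10%: 0.18 mm
- r = 20%: 0.26 mm

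The planned effect is 2 mm. Because the shift is random with mean zero, the unadjusted test keeps its nominal error rate under a common list.

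**Step 4: per-site lists with a test that ignores site.** Stratified allocation removes the site component from the difference, but the test still counts it in the standard error. With near-even splits within sites, true two-sided error = 2·P(Z > 1.96/√(1 − r)):

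- r = 5%: 1.96/0.975 = 2.01, error 4.4%
- r = 10%: 1.96/0.949 = 2.07, error 3.9%
- r = 20%: 1.96/0.894 = 2.19, error 2.8%

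All three lie below 5%.

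**Step 5: gain from adjusting for site.** Take the planned SDs to include site variation and replace 2.264 by 2.264·√(1 − r):

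| Per arm | Ignoring site | r = 5% | r = 10% | r = 20% |
|---|---|---|---|---|
| 22 | 81.7% | 83.6% | 85.5% | 89.3% |
| 30 | 92.0% | 93.2% | 94.4% | 96.4% |
| 35 | 95.4% | 96.2% | 97.0% | 98.3% |

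Spending 2 degrees of freedom on site lowers the adjusted figures by about 0.1 point or less.

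If the planned SDs describe variation within a site only, ignoring site costs power instead. By the normal approximation, power at 22 per arm falls from 83.4% to 81.5%, 79.4% or 74.6%. At 30 per arm it is still 91.5%, 90.1% or 86.4%.

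**The case against.** The strongest reply is that the article is silent on site and does not exclude it. Lists kept by clinic are compatible with a blocked scheme, and the regression in section 3 could include site among its unnamed variables. The article condenses a fuller protocol, where block sizes and covariates often sit. This stands. The point is therefore that neither step is stated to use site, and a reader who concludes that site has been left out goes further than the text.

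Two other stronger readings fail on the documents.

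- A reader might infer that aligner type is confounded with operator. The article does not say who plans, makes or fits the aligners, whether fabrication is local, how many operators or examiners there are, or how many patients each clinic contributes. Any imbalance has mean zero, so it does not bias the comparison.
- A reader might infer an inflated error rate. Under a common list the error rate is kept, and under per-site lists the test is conservative. These two costs are also alternatives and cannot both occur in the same trial.

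It is also fair to say that the benefit is small: at 30 to 35 per arm, adjustment adds about 1 to 4 points of power. Nothing here invalidates the planned comparison.

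What survives is that the article does describe the allocation and names blocking as its only restriction. Under either reading of that sentence there is a small avoidable cost, and one change removes both.

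**Conclusion.** The point holds as a recommendation to improve the design; it does not show an error. In a trial across three cities with examiner-graded indices among its listed end points, blocks stratified by site and a comparison that includes site are better than what is stated.

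The size is modest. With one common list there is about a 35% chance that some site splits 13:7 or worse, which adds noise only. With per-site lists and an unadjusted test, the true error is 4.4% down to 2.8%. Adjustment gains about 2 to 8 points of power at 22 per arm and 1 to 4 points at 30 per arm.

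These figures rest on an assumed 60 patients, equal sites and a site share of variance of 5% to 20%; the article gives neither site sizes nor a site share. The sample size of 22 per arm reproduces and is not called into question.

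**What to change.** - **Section 2.2:** state that the blocked 1:1 randomisation is stratified by site, with randomly varying block sizes and central allocation, so that the next assignment in a small site block cannot be guessed. If the lists are already kept by site, say so.
- **Section 3:** state that site is a factor in the model comparing the arms, both for space closure and for the examiner-scored indices.

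The cost is one sentence in each section, a regenerated allocation list if the current one is not by site, and 2 degrees of freedom for three sites or 3 for four. No extra patients, visits or staff are needed. The list must be changed before randomisation begins; the site term can be added at any time before the data are unblinded.

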### 1.2. Aim 2: Periodontal Health Status and Oral Microbiome

The second aim is to determine the periodontal health status during and after 3D clear aligners and thermoformed aligner therapy.

Clear aligner treatment (CAT) has been described as a secure and confident orthodontic procedure for patients. Recently, adult patients have sought a more aesthetic and comfortable orthodontic treatment than fixed appliances. To meet these needs, the treatment with transparent aligners (CAT) was introduced. The clear aligners cover the keratinized gingiva for a long period of time, and it is very important from a clinical point of view that CAT does not cause negative effects on periodontal tissues. Both conventional treatment and aligners cause a shift in the increase in anaerobes and periodontal pathogens and a decrease in commensal bacteria in the supra-gingival microbiome, but there are different types of aligners, i.e., 3D aligners and thermoformed aligners that can cause a periodontal reaction due to several factors such as the presence of systemic conditions, host resistance, and the amount and composition of dental plaque. Smoking and the patient’s lifestyle can compromise periodontal health and support. Oral hygiene procedures play a primary role in periodontal health during orthodontic treatment. Therefore, the objective is to determine the status of periodontal status and oral microbiome in 3D and thermoformed CAT.

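### Eligibility, stratification and named covariates all leave smoking, existing periodontal disease and recent antibiotics unaddressed, so the periodontal and microbiome comparisons lose precision and are open to chance imbalance

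*Protocol article*

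**What the plan says.** Section 2.2 of the protocol article sets out indications, contraindications and exclusions in some detail. Besides deciduous and mixed dentition, the exclusions read: "patients with systemic disease, developmental abnormalities, pregnant patients, mentally retarded patients and immunocompromised patients will not be included in the study". The contraindications are orthodontic and dental, beginning "Contraindications are crowding and spacing problems greater than 5 mm, anterior-posterior skeletal problems greater than 2 mm". Smoking, periodontal disease and antibiotics appear in neither list.

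Section 1.2 (Aim 2) discusses what drives a periodontal reaction under aligners and states: "Smoking and the patient’s lifestyle can compromise periodontal health and support". Section 2.3 puts plaque, bleeding, BPE, saliva and biofilm under the primary end point, and adds: "A standard estimation of the oral microbiome will be carried out using 16S ribosomal RNA gene sequencing analysis". The Abstract calls periodontal health and the microbiome secondary, with 7 days of follow-up.

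Periodontal status is measured at entry: "Periodontal health status will be assessed by basic periodontal examination (BPE), Periodontal screening and recording index (PSR index", together with OHIS and saliva and biofilm tests. Section 2.2 also says: "Pre- and post-operative samples of biofilm and saliva will be collected". Randomization is 1:1 in blocks, with no stratification factor given. Section 3 plans a regression without naming covariates. The Abstract gives 30 patients per group; section 3 says 70 will be recruited, which is 35 per arm at 1:1.

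**The concern.** The article itself identifies smoking as relevant to the outcomes of Aim 2, and then neither restricts it at entry nor provides for it in the allocation or the named analysis. Existing periodontal status is recorded, but no use of it for eligibility is stated. A site that follows the lists as written could enrol smokers, patients with existing periodontal disease and patients who have just finished an antibiotic course.

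At stake is the precision of the periodontal and microbiome comparisons. Each factor, if it matters for an outcome, adds variation within the arms. In a trial of this size it may also fall unevenly between them by chance. No Aim 2 outcome has a sample size of its own, so there is no planned reserve of power to absorb this.

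Recent antibiotics raise a further difficulty. If they suppress the flora (an assumption; the article does not say so), the baseline sample is itself distorted, and recovery within the 7-day window would be mixed with the aligner effect. Adjusting for a distorted baseline value would not fully repair that.

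**Working it through.** **1. The plan's own figure.** Section 3 gives means of 3 and 5 mm, SDs of 2.5 and 2.0, two-sided alpha 0.05 and power 0.80. The averaged SD is √((2.5² + 2.0²)/2) = 2.264 and the difference is 2. The normal approximation gives 21 per arm. The unequal-variance t-test has power 0.797 at 21 and 0.816 at 22, so the stated 22 per group reproduces. It covers space closure only.

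**2. Assumptions.** The article gives neither the prevalence p of these factors nor their effect e on any Aim 2 outcome. Both are assumed: p from 10% to 40%, and e from 0.5 to 1.0, in units of the outcome SD among patients alike on the factor.

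**3. Chance imbalance.** The number of patients with the factor in each arm is treated as an independent binomial(n, p). Blocking balances arm sizes, not the factor.

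| p | n = 30: differ by ≥3 (10 points) | n = 30: differ by ≥5 (17 points) | n = 35: differ by ≥4 (11 points) |
|---|---|---|---|
| 15% | 0.36 | 0.10 | 0.24 |
| 25% | 0.46 | 0.18 | 0.33 |
| 35% | 0.50 | 0.22 | 0.38 |

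With 35 per arm, 10 points is 3.5 patients, so the smallest qualifying difference is 4. Part of the fall between the two arm sizes comes from this rounding.

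**4. From imbalance to outcome.** The between-arm difference in prevalence has SD √(2p(1−p)/n), and the contrast shifts by e times the imbalance. With n = 30:
- p = 10%, e = 0.5: √(2 × 0.1 × 0.9/30) = 0.077; shift 0.039 SD, or 0.076 SD at 1.96 SDs of imbalance.
- p = 40%, e = 1: √(2 × 0.4 × 0.6/30) = 0.126; shift 0.126 SD, or 0.248 SD at 1.96 SDs.

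The difference detectable with 80% power at 30 per arm is (1.960 + 0.842) × √(2/30) = 0.72 SD. To shift the contrast that far at the 1.96-SD imbalance, one factor would need an effect of about 0.72/(1.96 × 0.126) = 2.9 SD at p = 40%, or 4.8 SD at p = 10%.

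**5. Loss of power.** An uncontrolled factor multiplies the outcome SD by √(1 + e²p(1−p)).
- p = 10%, e = 0.5: multiplier 1.011; power for 0.72 SD falls from 0.80 to 0.79.
- p = 25%, e = 1: multiplier √(1 + 0.1875) = 1.090; power 0.73.
- p = 40%, e = 1: multiplier √(1 + 0.24) = 1.114; power 0.71.
- Three independent factors, each p = 30% and e = 1: multiplier √(1 + 3 × 0.21) = 1.28; power about 0.59; shift at 1.96 SDs about 0.40 SD.

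**The case against.** The strongest reply is that randomization already protects the comparison: such factors produce noise and chance imbalance, not bias, and one factor alone costs only about 1 to 9 points of power. That stands. A reader might infer from the imbalance probabilities that these factors would overwhelm the aligner contrast. Step 4 does not support that: the largest single-factor shift considered is about 0.25 SD against a detectable 0.72 SD.

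Second, a reader might take the article's mention of antibiotics as an admission that prior use confounds the results. It is not. The sentence reads "This will help to answer the questions such as if any infection is present, which bacteria colonize, whether we should use antibiotics, etc", and concerns future use informed by the microbiology. The case for an antibiotic-free period rests on the logic of baseline sampling, not on a contradiction in the text.

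Third, it would be wrong to say that patients enter without a periodontal check. Section 2.2 requires a case history, examination and radiographs, and BPE and PSR are recorded at baseline. What is lacking is a statement of how those results bear on eligibility.

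Fourth, baseline indices and pre-treatment samples permit adjustment, and over 7 days stable characteristics partly cancel in within-patient change. This reduces the problem for periodontal status. It does not deal with antibiotics, and smoking is not named among the baseline items, although the case history may capture it.

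Fifth, an article may leave covariates and stratification factors to fuller documents, so their absence alone would be no finding. The eligibility lists, however, are written out, and they omit a factor that the same article calls harmful to periodontal health. Finally, excluding smokers would narrow generalisability; this is a fair objection, and the remedy below keeps them.

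**Conclusion.** The point holds for Aim 2 as a matter of precision and chance imbalance, and is worth correcting. The eligibility lists contain nothing on smoking, existing periodontal disease or recent systemic antibiotics, and no stated stratification factor or covariate handles them.

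The size is modest for one factor and becomes material only if several common, strong factors act together. The calculations depend on the assumed prevalences and effects, on independence of the factors in the three-factor case, and on which recruitment figure applies: 30 per arm in the Abstract or 35 implied by section 3. The reference power of 0.80 at 0.72 SD is a yardstick for the illustration; the article sets no power target for any Aim 2 outcome.

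The article does not support a claim of systematic bias between arms. Nor does it tie these factors to space closure, so the powered comparison is not shown to be affected.

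**What to change.** In the eligibility text of section 2.2:
- Add a period free of systemic antibiotics before the baseline saliva and biofilm samples. The sponsor sets its length, and deferral and re-screening are allowed.
- State how the BPE and PSR already recorded at baseline are used for eligibility, with the sponsor setting the code.

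In the design and analysis:
- Record smoking at entry and stratify the blocked randomization by it.
- Adjust the Aim 2 comparisons for smoking and for the baseline value of each outcome.

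The cost is a few deferred or failed screenings and one entry-form item. BPE, PSR and the baseline samples are already planned, and the stratify-and-adjust route for smoking loses no patients.
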